### Daily digital PAI EMI during the 6-week intervention phase

Digital PAI participants routinely receive an EMI component in conjunction with the 30-minute sessions, which are developed to boost the generalization of skills in real-time and within naturalistic settings. The EMI component starts immediately following each weekly session. Digital PAI participants receive notifications via their smartphones to practice brief PAI skills three times a day (morning, afternoon, and evening) during the 6-week intervention phase. All Digital PAI participants receive EMI messages at preset times and days, so the EMI represents a streamlined just-in-time adaptive interventions without skip logic to facilitate delivery standardization [99]. The EMI content prompt is thematically linked to the corresponding weekly session content to promote alignment between everyday exercises and the weekly Digital PAI content (e.g., appreciative joy, loving-kindness, self-compassion). Each prompt offers an actionable and succinct 1 to 2-minute exercise designed to foster proactive walkthroughs of Digital PAI content in naturalistic settings, thereby addressing the affective, behavioral, and cognitive pathways hypothesized to underlie improvements in positive mood states. This EMI approach aims to enhance ecological validity, optimize dosage, and reinforce newly learned ER skills across various daily contexts.

### Daily self-monitoring placebo control

Self-Monitoring Placebo participants receive a fully automated delivery of EMA prompts thrice daily (morning, afternoon, and evening) over the 6-week timeframe from baseline. Unlike the Digital PAI group, the Self-Monitoring Placebo does not consist of any psychotherapy content, skills-building practices, or treatment elements. Participants instead complete brief mood-monitoring self-reports designed to measure dynamic daily variations in emotional states. These EMAs include ratings on affective changes, current mood, emotional valence (positive, neutral, or negative), emotional preparedness, and the impact of daily events (e.g., activities, social interactions) on mood. Systematic variations in the EMA prompt content are introduced to minimize habituation (response set acquisition) and response burden while also sustaining participant engagement. This assessment-only method is used to adjust for nonspecific factors, such as attention, expectancy, and recurrent mood monitoring, thus enabling a strict validation test of the distinctive therapeutic effects of Digital PAI.

### Protocol adherence and engagement strategies

Participants will receive three Digital PAI or Self-Monitoring Placebo prompts per day across 6 weeks, totaling 126 prompts. Protocol adherence is operationally defined as the completion of at least 80% of these prompts (i.e., ≥ 101 of 126 prompts). Non-adherence is defined as missing key assessment batteries at baseline, mid-intervention, or post-intervention, or completing < 80% of all prompts. Beyond pro-rating reimbursement, other engagement strategies included giving automated reminders to participants and embedding brief 1 to 3-minute pre-recorded videos of the PI outlining the rationale of the Digital PAI techniques at the start of each section. Interactive components are also embedded in the weekly Digital PAI sessions, allowing participants assigned to the treatment group to engage in hands-on activities while learning the therapy content. Participants may withdraw from the study at any time without providing a reason and will not be required to complete any additional procedures.

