**Methods:**

This single-blind, two-arm, pragmatic RCT will recruit 1,200 community-dwelling adults with mild-to-moderate symptoms of anxiety or depression. Participants will be randomly assigned in a 1:1 allocation to either the Digital PAI or the Self-Monitoring Placebo as the placebo control across six weeks. Digital PAI comprises six weekly 30-minute self-guided online sessions coupled with thrice-daily ecological momentary interventions (EMIs) focusing on PA regulation. The Self-Monitoring Placebo offers non-therapeutic mood-tracking instructions three times daily. The same ecological momentary assessments (EMAs) are administered in both groups after each EMI prompt. Clinical outcome assessments are administered at baseline, mid-treatment (Week 3), post-treatment (Week 6), and 3-month, 6-month, and 12-month follow-ups. Primary outcomes are changes in anxiety and depression severity (Generalized Anxiety Disorder-7 [GAD-7] and Patient Health Questionnaire-9 [PHQ-9]). Secondary outcomes comprise anhedonia, emotion regulation, reward processing, and sleep quality. Randomly selected subsamples will provide wearable data. Analyses will harness multilevel modeling, generalized estimating equations, causal mediation, structural equation modeling, and precision medicine methods to evaluate treatment efficacy, change mechanisms, and moderators.

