### Weekly digital PAI 30-minute sessions during the 6-week intervention phase

Table 2 provides an overview of the Digital PAI content. PAT was initially developed by [name] and colleagues at the University of California, Los Angeles, to address difficulties in reward processing, specifically problems with wanting, liking, and learning about positive experiences [98]. The lead author ([name]) locally tailored this intervention for digital delivery and culturally tailored it for adults living in Singapore. Thus, the 6-week Digital PAI was adapted from the 15-week face-to-face, therapist-led PAT manual [98]. Digital PAI comprises 8 sequential online 30-minute sessions, each starting with a brief pre-recorded video to orient the user, and is provided over 6 weeks, each addressing key exercises linked to fostering PA and reducing anhedonia. The first few sessions teach participants about the characteristics of dampened positive emotions (Session 1) and offer psychoeducation on the aims, rationale, and structure of the Digital PAI, highlighting its scientifically informed approach (Sessions 2 and 3). In the following sessions, participants learn the skills to detect and change maladaptive patterns connecting actions, behaviors, and cognitions (Session 4). Session 5 equips participants with skill-building practices that foster engagement in independent and social activities that are experienced as congruent with one’s values, pleasurable, and rewarding, thereby enhancing everyday positive reinforcement. The Digital PAI further coaches participants to purposefully attend to, amplify, and maintain focus on positive experiences via generosity, gratitude, and related positive psychology–informed exercises (Session 6). Participants also learn to proactively create and consolidate positive moods through techniques such as positive reappraisal, reward sensitivity exercises, and positive reframing (Session 7). Finally, participants are encouraged to strengthen and sustain their learning by creating individualized skills consolidation plans and preparing for the lifelong practice of these skills in their daily routines beyond the formal Digital PAI program (Session 8). Between all sessions, EMIs will be provided to Digital PAI participants to help them apply their skills in multiple daily, real-world settings. Moreover, the Digital PAI offers guidance-on-demand, such that users can contact a trained study team member who will offer asynchronous coaching on users’ queries about applying skills learned in the program and related therapeutic processes.

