### Digital phenotyping in randomly selected subsamples

To supplement self-reported assessments, we included digital phenotyping through passive sensor wearables to objectively measure behavioral and physiological indices related to mental health. This method centers on assessing key outcomes, such as heart rate (HR) variability (HRV), step counts, and sleep-wake cycles, which have been shown to correlate with affect [100] and neurocognition [101]. During each baseline visit, participants are randomly selected to be given a consumer-grade Vivosmart^®^ passive sensor wearable (Garmin, Olathe, KS, USA) in conjunction with the “Garmin Connect” app embedded in the mEMA Ilumivu platform on their smartphones. Given budget constraints that allowed for the purchase of 25 waterproof wearables, participants from both treatment and control groups will be randomly selected. These participants will be invited to download, install, and allow the passive sensor to work together with the thrice-daily EMA surveys. These sensors will be worn continually by selected participants throughout the 6-week intervention phase, with encouragement to use them at least 70% of the time (i.e., ≥ 17 h daily, 5 days per week). This usage threshold will facilitate optimal multiple imputation of missing data from wearables [102]. These instructions were standardized by the PI and delivered by trained research personnel at the baseline visit. The wearable will capture the following dimensions of data during the 6-week intervention phase: geolocation [103], HRV-inter-beat intervals (IBIS) [104], HRV-root mean square of successive differences (RMSSD) [105], HRV-spectrum of frequencies [106], wear-time markers [107], and sleep actigraphy indicators [108, 109] (refer to Appendix B for more details). These wearable data, including geolocation, are captured to model context- and time-related patterns of everyday activity and mobility that can mediate or moderate the association between EMIs and changes in affective or clinical endpoints.

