### Statistical analysis plan

#### Data processing and missing data management

All preprocessing steps and data analyses will be conducted using the *R* software [113]. Using an intention-to-treat (ITT) approach, we will estimate between-group treatment efficacy for continuous and binary clinical outcomes [114]. A complier average causal effects (CACE) analysis will also be conducted to determine treatment efficacy between high- and low-potential engagers [115]. Before conducting the key data analyses, a series of preprocessing steps will be undertaken. These include anomaly diagnostics, assumption checks (e.g., linearity, multivariate normality), and random forest imputation of missing data. Random forest imputation with the *missRanger* package [116] will be used instead of multiple imputation because it better handles nonlinear associations and interactions and generates improved performance even under missing not-at-random (MNAR) conditions [117]. Sensitivity analyses will be conducted by examining outcomes under two alternative missing data management approaches, full information maximum likelihood (FIML) and multiple imputation [118]. The point estimates and 95% confidence intervals (CIs) of all effect sizes, Cohen’s *d* for continuous outcomes [119], as well as odds ratios [ORs] and risk ratios [RRs] for binary outcomes [120], will also be computed consistently.

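### Two adjacent adherence sentences classify the same participant differently, and the 70% wear-time rule works out at 50.6% of the time

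*Protocol article*

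**What the plan says.** All references are to the protocol article.

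- **Adherence.** Under 'Protocol adherence and engagement strategies': "Participants will receive three Digital PAI or Self-Monitoring Placebo prompts per day across 6 weeks, totaling 126 prompts". Then: "Protocol adherence is operationally defined as the completion of at least 80% of these prompts", with the count given as 101 of 126. The next sentence reads "Non-adherence is defined as missing key assessment batteries at baseline, mid-intervention, or post-intervention", and adds completion of fewer than 80% of prompts as an alternative condition.
- **Analysis that depends on engagement.** Under 'Data processing and missing data management': "A complier average causal effects (CACE) analysis will also be conducted to determine treatment efficacy", contrasting people likely to engage more with people likely to engage less. No complier definition is given there, and there is no reference back to the adherence section.
- **Wear time.** Under 'Digital phenotyping in randomly selected subsamples', selected participants wear a sensor throughout the six weeks, "with encouragement to use them at least 70% of the time". A parenthesis explains this as at least 17 h daily on 5 days per week. The purpose follows: "This usage threshold will facilitate optimal multiple imputation of missing data from wearables".
- **Sessions.** The abstract says "Digital PAI comprises six weekly 30-minute self-guided online sessions". The section on the weekly sessions says "Digital PAI comprises 8 sequential online 30-minute sessions", and Table 2 lists eight sessions in six weeks, three of them in Week 1.

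**The concern.** The two adherence sentences ought to be complements, and they are not. The first looks only at prompts. The second adds a condition on assessment batteries. The Week 3 and Week 6 batteries carry the GAD-7 and PHQ-9 (Table 1), so missing one is missing outcome data, a different matter from failing to use the intervention. An adherence rate reported from this section could follow either sentence. A complier variable built on the second sentence would also be tied to outcome missingness.

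The wear rule raises a separate problem: its percentage and its hours do not describe the same amount of wear. Because the threshold is justified by what imputation can support, the share of data it allows to be missing has to be stated correctly.

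**Working it through.** **1. Prompt cut-off (reproduces).** 3 prompts × 7 days × 6 weeks = 126. 0.80 × 126 = 100.8, so the smallest qualifying count is 101 (101/126 = 80.2%; 100/126 = 79.4%). The stated figures are right.

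**2. Classification under each sentence.**

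| Prompts completed | Batteries | First sentence | Second sentence |
|---|---|---|---|
| ≥ 101 | all completed | adherent | not non-adherent |
| ≥ 101 | one or more missed | adherent | **non-adherent** |
| ≤ 100 | either | not adherent | non-adherent |

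The sentences disagree in the second row only. For example, 120 of 126 prompts with no Week 3 battery is adherent by one sentence and non-adherent by the next.

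**3. Which batteries matter.** 'Study design' places randomization at the end of the baseline assessment, so almost nobody randomized can have missed the baseline battery. The conflict comes from Weeks 3 and 6.

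**4. Conditional effect on the CACE.** Suppose a standard ratio estimator, CACE = ITT effect / complier share. Let p be the share of the Digital PAI arm meeting the prompt rule, and q the share of those who miss a battery.

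- Prompt rule: ITT / p
- Second sentence: ITT / [p(1 − q)]
- Ratio of the two: 1/(1 − q), whatever the value of p

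The documents give neither p nor q. The values below are assumptions. The illustration uses p = 60% and an ITT effect of d = 0.20, the lower end of the range in 'Sample size and power'. Under the prompt rule, the CACE is then 0.20/0.60 = 0.33.

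| Assumed q | 1/(1 − q) | Inflation | CACE in the illustration |
|---|---|---|---|
| 5% | 1.05 | 5% | 0.20/0.57 = 0.35 |
| 10% | 1.11 | 11% | 0.20/0.54 = 0.37 |
| 25% | 1.33 | 33% | 0.20/0.45 = 0.44 |
| 40% | 1.67 | 67% | 0.20/0.36 = 0.56 |

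**5. Wear time (does not reproduce).** 17 h × 5 days = 85 h per week. A week has 24 × 7 = 168 h. 85/168 = 50.6%, or 510 of 1,008 h over six weeks. By contrast, 70% of the week is 0.70 × 168 = 117.6 h, equal to 16.8 h on all 7 days or 23.5 h on 5 days.

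The figure of 70% appears only when the two parts are taken separately: 17/24 = 70.8% of a day and 5/7 = 71.4% of days. Their product is again 50.6%. A participant who just meets the stated hours leaves 100 − 50.6 = 49.4% of the time unobserved, against the 30% that a true 70% rule would leave.

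**6. Session count.** The abstract, 'Study procedures' and 'Localization of the digital PAI' describe one 30-minute session per week for six weeks. The weekly-sessions section and Table 2 give eight. The number of sessions does not enter either adherence sentence.

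**The case against.** **The CACE may never use this rule.** The analysis section does not define compliers, does not point to the adherence section and does not name a ratio estimator. A complier definition is often left to a fuller plan. This stands. A reader might infer that the planned CACE is overstated, or overstated by a third; the documents support neither. The table above shows only what would follow if the second sentence were adopted, and the result depends on an unknown q. The 50% attrition allowed for in 'Sample size and power' makes missed batteries plausible, but it is not an estimate of q among people who complete their prompts.

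**Protocol adherence can legitimately include assessments.** The rule covers both arms and need not mean treatment receipt. That is fair, but it does not remove the contradiction: the sentence before defines the same term by prompts alone.

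**Lessons are left out of the rule.** A reader might call this an error because the lessons are part of the treatment. The placebo arm has no lessons, so a rule common to both arms cannot count them. Adding them would be a design preference.

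**The wear rule is loose wording, and about encouragement.** The separate readings (70.8% and 71.4%) probably explain where the 70% came from. The text does not say so, however, and a share of the time under wear throughout the six weeks most naturally means total time. A reader might infer that half the wearable data will be missing. That is too strong: 50.6% is a floor, reached only by someone who just meets the minimum, in a subsample limited by 25 devices.

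**Conclusion.** Two statements are wrong as written.

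First, the adherence and non-adherence sentences contradict each other for anyone with at least 101 prompts and a missed Week 3 or Week 6 battery, and the second counts missing outcome data as non-adherence. The 80% cut-off itself is correct. Any effect on the CACE is conditional: inflation of 5% to 67% for assumed q of 5% to 40%, if the second sentence defined compliers. That range also assumes a ratio estimator, the same ITT estimate under both definitions, and no effect of assignment among participants below the prompt cut-off.

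Second, the wear threshold stated as 70% of the time is 50.6% by its own hours, so the minimum can leave up to about 49% missing. This affects only the wearable data, including wear time where it is used as a covariate.

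The primary intention-to-treat comparison is unaffected by either. The six-versus-eight session discrepancy is real and needs reconciling, but it is not part of the adherence error.

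**What to change.** - **Adherence.** Keep the prompt-based rule (at least 101 of 126) as the single definition and make non-adherence its exact complement. Report completion of the Week 3 and Week 6 batteries separately, as retention.
- **CACE.** State the complier definition, and do not use battery completion in it.
- **Wear time.** Make the percentage and hours agree. One wording that keeps the present hours is about 70% of hours on about 70% of days, that is, a minimum of 51% of total time. Match the imputation rationale to a minimum that can leave about 49% missing.
- **Sessions.** Reconcile the count across the abstract, 'Study procedures', 'Localization of the digital PAI', the weekly-sessions section and Table 2.

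**Cost.** The adherence, CACE and wear-rule changes are wording only if the present wear hours are kept. 'Study procedures' already describes a backend engagement log for both arms. Changing the wear hours would cost more, because the standardized participant instructions would change while enrolment is under way. Settling the adherence rule now, while the analyst is blinded, avoids a later choice between two definitions.

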### Brief EMAs in both digital PAI and self-monitoring placebo groups

Immediately after each EMI prompt in the Digital PAI group and each EMA prompt in the Self-Monitoring Placebo group, participants fill in a brief EMA capturing momentary emotional states and symptom severity on a 10-point Likert scale (1 = *not at all* to 10 = *very much*). This EMA captures 10 emotional states experienced since the most recent prompt, which can be categorized as *positive* (calm, energetic, happy, optimistic, and relaxed) or *negative* (anxious, depressed, fatigued, frustrated, and worried). These EMAs are delivered thrice daily, corresponding with the delivery of the EMI or EMA prompts, thus offering granular, high-frequency data on daily emotional processes over the 6-week intervention phase. It also facilitates the modeling of between-day and within-day variations in affective experiences, which can be used to determine the proximal effects of the Digital PAI versus the Self-Monitoring Placebo, as well as to explore trajectories, moderators, and mediators. By inserting the same EMA in both groups, this approach enables a direct comparison of proximal affective changes, reduces confounders, and ensures consistency in methods.

### Digital phenotyping in randomly selected subsamples

To supplement self-reported assessments, we included digital phenotyping through passive sensor wearables to objectively measure behavioral and physiological indices related to mental health. This method centers on assessing key outcomes, such as heart rate (HR) variability (HRV), step counts, and sleep-wake cycles, which have been shown to correlate with affect [100] and neurocognition [101]. During each baseline visit, participants are randomly selected to be given a consumer-grade Vivosmart^®^ passive sensor wearable (Garmin, Olathe, KS, USA) in conjunction with the “Garmin Connect” app embedded in the mEMA Ilumivu platform on their smartphones. Given budget constraints that allowed for the purchase of 25 waterproof wearables, participants from both treatment and control groups will be randomly selected. These participants will be invited to download, install, and allow the passive sensor to work together with the thrice-daily EMA surveys. These sensors will be worn continually by selected participants throughout the 6-week intervention phase, with encouragement to use them at least 70% of the time (i.e., ≥ 17 h daily, 5 days per week). This usage threshold will facilitate optimal multiple imputation of missing data from wearables [102]. These instructions were standardized by the PI and delivered by trained research personnel at the baseline visit. The wearable will capture the following dimensions of data during the 6-week intervention phase: geolocation [103], HRV-inter-beat intervals (IBIS) [104], HRV-root mean square of successive differences (RMSSD) [105], HRV-spectrum of frequencies [106], wear-time markers [107], and sleep actigraphy indicators [108, 109] (refer to Appendix B for more details). These wearable data, including geolocation, are captured to model context- and time-related patterns of everyday activity and mobility that can mediate or moderate the association between EMIs and changes in affective or clinical endpoints.

Data from the wearable device will be automatically updated, synced, and uploaded to the mEMA Sense software, eliminating the need for participants to manually transfer data. Nonetheless, they will be trained during the baseline visit and reminded in subsequent email exchanges with study coordinators on how to manually trigger syncing in case the automatic upload fails at any point during the 6-week intervention phase. Finally, these participants will return the wearable to the research personnel after the 6-week intervention phase.

### Proximal outcomes

Our trial will assess the comparative efficacy of Digital PAI versus Self-Monitoring Placebo in terms of moment-to-moment changes in positive and NA states, serving as proximal outcomes. The brief EMAs will serve as proximal outcome measures to evaluate the immediate effects of treatment. This approach enables fine-grained modeling of immediate-term and within-day emotional changes, which likely indicate the initial skill-building of reward processing offered by the Digital PAI. These proximal outcomes may serve as key treatment mediators of downstream functional and symptom improvements, potentially informing clinicians and policymakers about essential treatment mechanisms. Moreover, capitalizing on metadata engagement metrics, including app usage patterns, EMI prompt completion rates, response times, and time-of-day effects, may facilitate process-level evaluation to optimize EMI delivery, dosing, and timing. Collectively, these proximal metrics provide a comprehensive approach to modeling both actions and affective states associated with short-term treatment engagement and efficacy.

